**Subgroup and sensitivity analyses**

We will calculate the risk of overall arrhythmia by sex, age at index date (<18, 18-<40, 40-<60, and ≥60), calendar period at index date (1969-1989, 1990-1999, 2000-2009, and 2010-2019), educational attainment (0-9 y, 10-12 y, ≥13 y, and “missing”), and number of healthcare visits (0, 1, 2-3, and ≥4). We will also explore the associations by location for CD, by extent for UC according to the Montreal classification, and by occurrence of primary sclerosing cholangitis or other extraintestinal manifestations (see below **Table 2** for ICD codes) [3].

Several sensitivity analyses will be conducted. **First,** due to lack of detailed data on smoking, we will restrict the analysis to those without COPD (a proxy for heavy smoking) before index date. **Second,** we will restrict the analysis to individuals with data available on educational attainment. **Third,** given that the Prescribed Drug Register is available since July 2005, we will restrict the analysis to individuals with index date later than 1 January 2006 and apply the statistical models further adjusting for the above mentioned cardiovascular related medications. **Fourth,** we will repeat the main analysis after excluding individuals with incident arrhythmias recorded within 1 year or within 3 years of follow-up after index date. **Fifth,** we will compare patients with IBD with their IBD-free full siblings after conditioning on family identifier and adjusting for birth year, sex, county of residence, calendar year, and all above mentioned covariates.

Data analyses will be performed using SAS version 9.4 (SAS Institute Inc, Cary, NC), Stata (version 16.1; Stata Corp LP, College Station, TX), and R version 3.6.0. A two-sided *P* ≤ 0.05 will be considered statistically significant.

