**Follow-up and ascertainment of outcome**

Individuals with previous arrhythmia (see below **Table 3** for ICD codes) before index date will be excluded. Follow-up will start at index date until incident diagnosis of arrhythmias, emigration, death, or December 31, 2019, whichever occurs first. Reference individuals or IBD-free full siblings will also be censored when receiving a diagnosis of IBD during follow-up. Individuals with an incident arrhythmia will be identified from the NPR, considering both primary and secondary diagnosis. The primary outcome is the incidence of overall arrhythmias. The secondary outcomes are the incidences of atrial fibrillation/flutter, bradyarrhythmias, other supraventricular arrhythmias, and ventricular arrhythmias/cardiac arrest. If one individual is diagnosed with more than one of the secondary outcomes, this individual will contribute to each outcome with the respective diagnosis date.

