**STATISTICAL ANALYSES**

We will report incidence rate (IR) and IR difference, together with 95% confidence intervals (CIs) for all outcomes. To estimate the average and temporal patterns of hazard ratios (HRs) and 95% CIs for incident arrhythmias in relation to IBD, flexible parametric survival models will be applied to allow the effect of IBD to vary over time (time-varying effect)[8]. Time since index date will be used as the underlying time scale. Standardized cumulative incidence and its differences of arrhythmia will be estimated. We will report the cumulative incidence difference at 1 year, 5 years, 10 years, and 25 years after index date. In the population matched cohort, we will condition the analyses on the matching variables (birth year, sex, county of residence, and calendar year) in model 1, and additionally adjust for country of birth, educational attainment, number of healthcare visits, ischemic heart disease, heart failure, stroke, hypertension, diabetes, obesity, dyslipidemia, chronic kidney disease, and COPD in model 2.

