**Ethics consideration**

This study is approved by the Stockholm Ethics Review Board (2014/1287-31/4 and 2018/972-32).

*Non-prespecified Analyses (Analyses according to comments from external reviewers):*

- To assess the influence of cardiovascular-related comorbidities on the associations, we excluded those with cardiovascular-related comorbidities before the index date from the analysis.
- In a sensitivity analysis, we further adjusted for autoimmune thyroid disease in the model to assess its influence on the associations.

| **Table 1. International Classification of Disease (ICD) codes and SNOMED codes defining inflammatory bowel disease (IBD) ^a^**. | | | | | |
| --- | --- | --- | --- | --- | --- |
|  | ICD-7 (1964-1968) | ICD-8 (1969-1986) | ICD-9 (1987-1996) | ICD-10 (1997-) | SNOMED codes ^b^ |
| Ulcerative colitis (UC) | 572,20; 572,21; 578,03 | 563,1; 563,10; 569,02; 569,04 | 556 | K51 | D6255 or M41, M42, M43, M44, M463, or M47 |
| Crohn’s disease (CD) | 572,00; 572,09 | 563,00 | 555 | K50 | D6216 or M41, M42, M43, M44, M463, or M47 |
| IBD unclassified (IBD-U) | UC + CD | UC + CD or 563; 563,0; 563,9; 563,98; 563,99 | UC + CD | K52.3 | D6214 or M41, M42, M43, M44, M463, or M47 |
| ^a^ ≥1 ICD code for IBD plus a relevant biopsy code has a positive predictive value of 95% [9,10]. | | | | | |
| ^b^ D codes are diagnostic codes but listed under morphology in pathology registers; D6255 for example is the diagnostic code for UC. SNOMED codes starting with "M"; M41 for example refers to all codes starting with "M41". | | | | | |
| Because definitions of exposure should not “look into the future”, IBD subtypes were defined in accordance with the first two diagnostic codes only (i.e., no information after start of follow-up contributed to the subtype definition). For individuals with one ICD code for IBD and one unspecific SNOMED code (i.g., “M…”), the IBD subtype was determined by the ICD code in the patient register only. In a recent paper [11], we report that 18% of incident patients with IBD in the Swedish patient register during 2002-2014 were classified as another IBD subtype at some point during follow-up. | | | | | |

| **Table 2. ICD codes assigned for phenotypes of inflammatory bowel disease** | |
| --- | --- |
| Montreal classification | Diagnostic codes |
| Crohn’s disease location ^a^ |  |
| Ileal (L1) | K50.0 |
| Colonic (L2) | K50.1 |
| Ileocolonic or location not defined (L3/LX) | K50.8, K50.9 |
| Ulcerative colitis extent ^a^ |  |

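### The 1- and 3-year lag analyses delete early arrhythmia cases but do not move the start of follow-up, so their absolute measures include person-time in which no event can occur

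*SAP*

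**What the plan says.** Four statements in the SAP bear on this point.

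- Subgroup and sensitivity analyses, fourth item: "we will repeat the main analysis after excluding individuals with incident arrhythmias recorded within 1 year or within 3 years of follow-up".
- Follow-up and ascertainment of outcome: "Follow-up will start at index date until incident diagnosis of arrhythmias, emigration, death, or December 31, 2019, whichever occurs first".
- Statistical analyses, time scale: "Time since index date will be used as the underlying time scale".
- Statistical analyses, outputs: "We will report incidence rate (IR) and IR difference, together with 95% confidence intervals (CIs) for all outcomes", and "We will report the cumulative incidence difference at 1 year, 5 years, 10 years, and 25 years after index date". HRs come from flexible parametric models in which the IBD effect may change with time.

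The fourth item gives no separate start of follow-up. It also gives no rule for people who die, emigrate or are otherwise censored inside the lag.

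**The concern.** A lag analysis asks whether an association persists once the period around diagnosis is set aside, when extra contact with care may bring existing arrhythmias to light. To answer that on the absolute scale, events and time at risk in the lag must both be removed. The rule as written removes the events and keeps the time.

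The plan has no other analysis that removes early follow-up. If rates and risk differences are reported from this one, they will be smaller than in the main analysis for a mechanical reason. A reader could take the fall as a sign that early detection explained part of the excess.

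**Working it through.** The SAP states no event rate, cohort size or expected follow-up, so there is no figure of its own to reproduce. The direction follows from the text; the size needs assumptions.

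**Assumed inputs (none from the SAP).** Constant hazards. Reference arrhythmia rate 8 per 1000 person-years and HR 1.3, so the IBD rate is 10.4. Death or censoring 10 (reference) and 12 (IBD) per 1000 person-years. Maximum follow-up T of 5, 10 or 25 years. The HR is constant, so the example contains no detection bias. The true rate difference is 10.4 − 8.0 = 2.40 per 1000.

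**Formulas, per person entering.** With arrhythmia hazard λ, death or censoring hazard μ, s = λ + μ and lag L:

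- Events after the lag: E = (λ/s)(e^(−sL) − e^(−sT)).
- Person-years from index, everyone: (1 − e^(−sT))/s.
- Person-years of those deleted: λ[1 − e^(−sL)(1 + sL)]/s².
- As written: rate = E / (person-years from index − deleted person-years).
- Landmark: rate = E / [(e^(−sL) − e^(−sT))/s], which equals λ.

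**Worked case, T = 10, L = 3.**

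- IBD, s = 0.0224: E = (0.0104/0.0224)(0.93501 − 0.79932) = 0.0630. Person-years as written: 8.9591 − 0.0448 = 8.9144. Rate: 0.0630/8.9144 = 7.07 per 1000. Landmark: 0.0630/6.0577 = 10.40.
- Reference, s = 0.018: E = (0.008/0.018)(0.94743 − 0.83527) = 0.04985. Person-years as written: 9.1517 − 0.0347 = 9.1169. Rate: 0.04985/9.1169 = 5.47 per 1000. Landmark: 0.04985/6.2312 = 8.00.
- Rate difference as written: 7.07 − 5.47 = 1.60, against 2.40 with the landmark. That is 33% too small.

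**All cases, rate difference per 1000 person-years (true value 2.40).**

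| Maximum follow-up | 1-year lag as written | 3-year lag as written |
| --- | --- | --- |
| 5 years | 1.89 (21% low) | 0.92 (62% low) |
| 10 years | 2.12 (12% low) | 1.60 (33% low) |
| 25 years | 2.26 (6% low) | 1.99 (17% low) |

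With the reference rate varied from 4 to 16 per 1000 and the HR set to 1.15 or 1.3, the shortfall is 5-22% for the 1-year lag and 16-62% for the 3-year lag.

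**Cumulative incidence difference (same rates, competing events ignored).** With the origin left at index, risk accrues only over t − L years, so the difference is e^(−0.008(t−L)) − e^(−0.0104(t−L)), and zero for t ≤ L. At 1 year it is 0 under either lag, against 0.24 percentage points without deletion. At 5 years it is 0.93 (1-year lag) and 0.47 (3-year lag), against 1.15 without deletion. A smooth parametric fit would return a value near zero at 1 year rather than exactly zero.

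**Relative measures.** Cox fits to one simulated cohort of 12,000 gave the same HR under the written rule and the landmark: 1.299 for the 1-year lag and 1.325 for the 3-year lag. This is expected. Nobody has an event inside the lag, so the risk sets at the remaining event times are identical. In the cases tabulated above the crude rate ratio moves only from 1.300 to 1.291-1.297.

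**The case against.** Three objections deserve weight.

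**The unchanged origin is inferred.** The fourth item never says when person-time starts. A reader might infer that the plan expressly keeps follow-up from index here; it does not. The reading comes from combining that item with the follow-up and time-scale rules. Still, an instruction to repeat the main analysis with some people removed has no other literal meaning. The authors may have intended a landmark, but the text does not say so.

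**Absolute outputs for the lag analysis are also inferred.** The SAP promises rates and rate differences for all outcomes, not explicitly for each sensitivity analysis. If only HRs will be reported, most of the problem goes away, but the plan should then say so.

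**The landmark is not directly comparable with the main analysis either.** If the hazard rises with time, rates counted from year 3 exceed those counted from index. In one assumed scenario (reference hazard 4 + 0.6t per 1000, mean follow-up about 17.8 years, HR highest early), the reference rate was 11.5 in the main analysis, 10.7 under the written 3-year rule and 12.8 from the landmark. For the rates themselves, the written rule lay closer to the main analysis. The rate difference was about 1.3 in the main analysis, 1.0 as written and 1.3 from the landmark. The caution about comparing rates stands; it does not rescue the written rule.

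Two stronger readings are not supported. One is that the lagged association is biased: the average HR is essentially the same under both rules. The other is that the plan breaks its own principle that "definitions of exposure should not “look into the future". That note to Table 1 concerns how IBD subtype is assigned, not who enters a sensitivity analysis.

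**Conclusion.** The point holds as a defect of limited scope that should be corrected. Followed literally, the rule puts event-free time into the denominators of the lag analyses and lowers their absolute measures. It makes the 1-year cumulative incidence difference about zero and leaves any HR shown inside the lag without events. These directions do not depend on the assumed rates.

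The sizes do. At a reference rate of 8 per 1000 and HR 1.3, the shortfall in the rate difference runs from 6% to 21% (1-year lag) and from 17% to 62% (3-year lag), and is largest when follow-up is short. No single percentage is a property of this plan. How far the fitted HR curve would be distorted inside the lag has not been quantified.

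The primary estimate, the main cumulative incidences and the average lagged HR are not affected.

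**What to change.** Reword the fourth sensitivity analysis as a landmark analysis:

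- In both groups, start follow-up at index plus 1 year, and in a second run at index plus 3 years.
- Include only people who at that date are alive, living in Sweden, uncensored and free of arrhythmia.
- Count person-time and cumulative incidence from the landmark, and describe the latter as conditional on being at risk then.
- Show no HR inside the lag.
- State whether rates and cumulative incidences will be reported for this analysis or HRs only.

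The cost is a sentence or two in the SAP and a changed start date in the code. People who die or are censored inside the lag also leave the analysis. Landmark rates should carry a note that they are not to be compared directly with main-analysis rates if the hazard rises over time.

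### The medication and sibling sensitivity analyses each change the patient set together with the adjustment or the comparator, and no same-set reference result is specified for either

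*SAP*

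**What the plan says.** Main analysis (SAP, Statistical Analyses): population-matched cohort, model 1 conditioned on the matching variables. Model 2 will "additionally adjust for country of birth, educational attainment, number of healthcare visits, ischemic heart disease, heart failure, stroke" and the remaining listed comorbidities. It has no separate drug terms. In the same section, "flexible parametric survival models will be applied to allow the effect of IBD to vary over time", with time since index date as the time scale.

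Third sensitivity analysis (SAP, Subgroup and sensitivity analyses): "we will restrict the analysis to individuals with index date later than 1 January 2006" and, in the same sentence, "apply the statistical models further adjusting for the above mentioned cardiovascular related medications". The reason given is that the Prescribed Drug Register starts in July 2005.

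Fifth sensitivity analysis (same section): "we will compare patients with IBD with their IBD-free full siblings after conditioning on family identifier". The four matching variables enter that model as covariates, together with every covariate named earlier in the plan. The SAP section on reference individuals and siblings requires both kinds of comparator to be alive, resident in Sweden, and free of IBD and arrhythmia at the index date.

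The SAP does not state a run of model 2 without drugs in the post-2006 cohort, or a population-reference comparison limited to the patients who have an eligible sibling.

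**The concern.** Adding drugs to a model, or replacing population references with siblings, is informative only against a reference result in which everything else is held fixed. In both analyses a second thing moves: the patients. The nearest stated reference is the main HR from the full cohort, with index dates from 1969 onward.

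The plan itself treats the effect as possibly non-constant: it models a time-varying effect and examines age and calendar-period strata. If the effect does vary, an average HR depends on who is in the set and how long they are followed. A difference from the main HR could then be read as the influence of drugs or of shared family factors when it reflects only the different set. Equally, two effects could cancel and suggest a robustness that is not there.

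**Working it through.** The SAP gives no HR, event count or baseline rate, so there is no figure to reproduce. The check is what changes in each analysis, then whether the patient set alone can move an average HR.

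**1. What changes relative to main model 2**

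| | Patients | Comparator and conditioning | Adjustment | Same-set reference stated? |
|---|---|---|---|---|
| Third analysis | index date after 1 January 2006 | unchanged | model 2 plus seven drug groups | no |
| Fifth analysis | those with an eligible full sibling (implied by conditioning on family) | full siblings; family identifier | matching variables become covariates, plus all earlier covariates | no |

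**2. Length of follow-up.** Follow-up ends on 31 December 2019. The maximum is 2020 − 1969 = 51 years for the full cohort and 2020 − 2006 = 14 years for the restricted one.

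**3. Two-period illustration (all inputs assumed).** Average HR = exp[w·ln(HR early) + (1 − w)·ln(HR later)], where w is the share of events in the early period. Assume w = 0.1 in the long cohort and 0.3 in the restricted one, with no drug confounding.

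- HR 2.0 early, 1.15 later: exp(0.1·ln 2.0 + 0.9·ln 1.15) = 1.22; exp(0.3·ln 2.0 + 0.7·ln 1.15) = 1.36. The average rises.
- Reversed, 1.15 early and 2.0 later: exp(0.1·ln 1.15 + 0.9·ln 2.0) = 1.89; exp(0.3·ln 1.15 + 0.7·ln 2.0) = 1.69. The average falls.
- HR 1.2 in both periods: 1.20 and 1.20. No shift.

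**4. Range over less schematic assumptions.** Assume uniform entry to the end of 2019, a baseline arrhythmia hazard of 0.008 per year growing at 0% or 5% per year, competing mortality of 0.01 per year, and no drug confounding. Log HRs are averaged with weights equal to (share still under administrative follow-up) × (event-free survival) × (baseline hazard).

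| Assumed HR at <1, 1–<5, 5–<10, ≥10 years | Growth | Index from 1969 | Index from 2006 |
|---|---|---|---|
| 1.2 throughout | 0% or 5% | 1.200 | 1.200 |
| 1.5, 1.25, 1.15, 1.1 | 0% | 1.154 | 1.239 |
| same | 5% | 1.131 | 1.225 |
| 2.0, 1.3, 1.15, 1.1 | 0% | 1.180 | 1.317 |
| same | 5% | 1.145 | 1.290 |
| 2.5, 1.4, 1.2, 1.05 | 0% | 1.188 | 1.423 |
| same | 5% | 1.129 | 1.382 |

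**5. Sibling set, with no familial confounding (all inputs assumed).** Suppose 30% of main-set patients are aged 60 or over and give 65% of events, and that the HR is 1.4 below 60 and 1.1 from 60. Main average: exp(0.65·ln 1.1 + 0.35·ln 1.4) = 1.20. If a share p of the sibling set is 60 or over, their event share is e = (0.65·p/0.3) / (0.65·p/0.3 + 0.35·(1 − p)/0.7).

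- p = 0.2: e = 0.433/(0.433 + 0.400) = 0.52; average HR 1.24.
- p = 0.1: e = 0.217/(0.217 + 0.450) = 0.325; average HR 1.29.
- p = 0.4: e = 0.867/(0.867 + 0.300) = 0.743; average HR 1.17.

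The document does not say how the sibling set differs from the whole cohort, so both directions are shown. With equal HRs in the two age groups there is no shift.

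**6. Bridges already in the plan.** The calendar strata include 2000–2009, which straddles 2006, and 2010–2019, which lies wholly inside the restricted set. HRs by time since index can be compared at equal follow-up. Both help the medication analysis. No stratum corresponds to the patients with an eligible sibling.

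**The case against.** The strongest objection is that the SAP never says it will attribute a difference to drugs or to family factors. It lists these only as sensitivity analyses, so nothing is contradicted. That stands: this is a gap in what the analyses can show.

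Second, the temporal HR patterns and the 2010–2019 stratum already allow part of the comparison. That also stands for the medication analysis. Time-specific HRs remove the follow-up-length mechanism, but not other differences between earlier and later index dates. The wording on applying the models with further adjustment may even be meant to include the unadjusted step, but it does not say so. If it is meant, one clause settles it.

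Third, register availability forces the 2006 restriction. True, but that does not prevent fitting model 2 without drugs in the same cohort.

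Two stronger readings are tempting. A reader might infer that patients with an eligible sibling are younger or more recent than the rest. The SAP states no coverage limit for the Multi-Generation Register, and the conditions of being alive, resident and free of IBD and arrhythmia apply to population references as well. A reader might also expect the sibling HR to fall below the main HR. The document gives no basis for that direction, and the illustrations go either way.

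**Conclusion.** The concern holds as a gap in interpretability. In the third and fifth sensitivity analyses the patient set changes together with the adjustment or the comparator, and no same-set result is specified. The medication half is the stronger: the restriction is explicit and shortens maximum follow-up from about 51 to 14 years. The sibling half rests on the implication that conditioning on family limits the informative patients, and nothing in the plan bridges it.

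Size and direction cannot be derived from the SAP. Under the assumed inputs, shifts run from none (constant HR) to about 0.25 on the HR scale (1.129 to 1.382), with no confounding at all. The illustrations show that the patient set alone can move the HR; they do not predict that it will. The primary HR is unaffected.

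**What to change.** 1. In the cohort with index date after 1 January 2006, report model 2 without and with the medications side by side.
2. Refit the population-reference model 2 in the IBD patients who contribute to the sibling analysis, with their own matched references, and show it beside the sibling HR. Use the same covariate set in both and state whether the drugs are in it. The present reference to all earlier covariates leaves this open, and drug data exist only from July 2005. If the covariates differ, the contrast does not isolate the comparator.
3. State that any comment on drugs or familial factors rests on these within-set contrasts and not on the distance from the main HR.

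The SAP's modification history places the analyses after version 2 and up to January 2023, so these runs should be labelled as added later, as the SAP already does for the analyses requested by external reviewers. The cost is two model runs and two table rows, with no new data and no change to the primary analysis.

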**Ethics consideration**

This study is approved by the Stockholm Ethics Review Board (2014/1287-31/4 and 2018/972-32).

*Non-prespecified Analyses (Analyses according to comments from external reviewers):*

- To assess the influence of cardiovascular-related comorbidities on the associations, we excluded those with cardiovascular-related comorbidities before the index date from the analysis.
- In a sensitivity analysis, we further adjusted for autoimmune thyroid disease in the model to assess its influence on the associations.

| **Table 1. International Classification of Disease (ICD) codes and SNOMED codes defining inflammatory bowel disease (IBD) ^a^**. | | | | | |
| --- | --- | --- | --- | --- | --- |
|  | ICD-7 (1964-1968) | ICD-8 (1969-1986) | ICD-9 (1987-1996) | ICD-10 (1997-) | SNOMED codes ^b^ |
| Ulcerative colitis (UC) | 572,20; 572,21; 578,03 | 563,1; 563,10; 569,02; 569,04 | 556 | K51 | D6255 or M41, M42, M43, M44, M463, or M47 |
| Crohn’s disease (CD) | 572,00; 572,09 | 563,00 | 555 | K50 | D6216 or M41, M42, M43, M44, M463, or M47 |
| IBD unclassified (IBD-U) | UC + CD | UC + CD or 563; 563,0; 563,9; 563,98; 563,99 | UC + CD | K52.3 | D6214 or M41, M42, M43, M44, M463, or M47 |
| ^a^ ≥1 ICD code for IBD plus a relevant biopsy code has a positive predictive value of 95% [9,10]. | | | | | |
| ^b^ D codes are diagnostic codes but listed under morphology in pathology registers; D6255 for example is the diagnostic code for UC. SNOMED codes starting with "M"; M41 for example refers to all codes starting with "M41". | | | | | |
| Because definitions of exposure should not “look into the future”, IBD subtypes were defined in accordance with the first two diagnostic codes only (i.e., no information after start of follow-up contributed to the subtype definition). For individuals with one ICD code for IBD and one unspecific SNOMED code (i.g., “M…”), the IBD subtype was determined by the ICD code in the patient register only. In a recent paper [11], we report that 18% of incident patients with IBD in the Swedish patient register during 2002-2014 were classified as another IBD subtype at some point during follow-up. | | | | | |

| **Table 2. ICD codes assigned for phenotypes of inflammatory bowel disease** | |
| --- | --- |
| Montreal classification | Diagnostic codes |
| Crohn’s disease location ^a^ |  |
| Ileal (L1) | K50.0 |
| Colonic (L2) | K50.1 |
| Ileocolonic or location not defined (L3/LX) | K50.8, K50.9 |
| Ulcerative colitis extent ^a^ |  |
| Proctitis (E1) | K51.2 |
| Left-sided colitis (E2) | K51.3; K51.5 |
| Extensive colitis (E3) | K51.0 |
| Extent not defined (EX) | K51.4; K51.8; K51.9 |
| Primary sclerosing cholangitis ^b^ | ICD-9 (1987-1996): 576B |
|  | ICD-10 (1997-): K830 |
| Other extraintestinal manifestations | ICD-9: 695C, 364, 713B, 720A, 720C, 720W, 720X |
|  | ICD-10: L52, L88, L98.2, H20, M07.4, M07.5, M07.6, M09.1, M09.2, M45, M460, M461,, M468, M469, M139, M255 |
| ^a^ Validated definitions and diagnostic codes [3] used to define Crohn’s disease and ulcerative colitis according to the Montreal classification since the start of use of the ICD-10 in Sweden (1997-). All codes are captured in the Swedish National Patient Register (prospectively recorded in routine clinical practice). | |
| ^b^ We restricted our use to ICD-9 and ICD-10 codes since we believe that earlier ICD codes for extraintestinal inflammation are less reliable, particularly for primary sclerosing cholangitis (PSC). The validity of the PSC codes has not formally been tested in Sweden. But according to [name] ([contact], a renowned researcher in PSC epidemiology at Karolinska Institutet and also the PI for a large Swedish PSC-cohort and biobank), the impression is that the sensitivity and positive predictive value of K830A for identifying PSC in IBD in the National Patient Register is not perfect, but the nationwide prevalence of PSC in IBD in the National Patient Register is roughly as would be expected, based on the prevalence in detailed patient cohorts at the university hospitals. | |

| **Table 3. Definitions of primary and secondary outcomes** | |
| --- | --- |
| Outcome | Definition |
| Primary outcome |  |
| Overall arrhythmia | Composite outcome including any individual outcomes from 1a-1d. |
| Secondary outcomes |  |
| 1a. Atrial fibrillation/flutter | ICD-8: 427,92 |
|  | ICD-9: 427D |
|  | ICD-10: I48 |
| 1b. Bradyarrhythmias | ICD-8: 427,20; 427,27; 427,28; 427,29 |
|  | ICD-9: 426A; 426B; 426G; 426X |
|  | ICD-10: I441; I442; I452; I453; I459; I495 |
| 1c. Other supraventricular arrhythmias | ICD-8: 427,90 |
|  | ICD-9: 426H; 427A |
|  | ICD-10: I456; I471 |
| 1d. Ventricular arrhythmias/cardiac arrest | ICD-8: 427,91; 795,99 |
|  | ICD-9: 427B; 427E; 427F; 798B; 798C |
|  | ICD-10: I460; I461; I469; I470; I472; I490; R960 |

| **Table 4. Definitions of comorbidities** | |
| --- | --- |
| **Comorbidity** | **Definition** |
| Ischemic heart disease | ICD-8: 410-414 |
|  | ICD-9: 410-414 |
|  | ICD-10: I20-25 |
| Heart failure | ICD-8: 428 |
|  | ICD-9: 428 |
|  | ICD-10: I42; I50 |
| Stroke | ICD-8: 431-434 |
|  | ICD-9: 431-434 |
|  | ICD-10: I61-64 |
| Hypertension | ICD-8: 400-404 |
|  | ICD-9: 401-405 |
|  | ICD-10: I10-I15 |
|  | Medication ATC codes: see antihypertensive medications in Table 5 |
| Obesity | ICD-8: 277 |
|  | ICD-9: 278A, 278B |
|  | ICD-10: E65-66 |
| Diabetes | ICD-8: 250 |
|  | ICD-9: 250 |
|  | ICD-10: E10-E14, O24 |
|  | Medication ATC codes: see antidiabetic medications in Table 5 |
| Dyslipidemia | ICD-8: 279 |
|  | ICD-9: 272 |
|  | ICD-10: E78 |
|  | Medication ATC codes: C10 |
| Chronic kidney disease | ICD-8: 585, 586, Y29,01 |
|  | ICD-9: 585, 586, 753B, V42A, V45B, V56 |
|  | ICD-10: N18, N19; N26; T824; Y841; Q61; Z49; Z992; Z940 |
| Chronic obstructive pulmonary disease (COPD)  (only if patient diagnosed ≥40 year) | ICD-8: 491, 492 |
|  | ICD-9: 491, 492, 496 |
|  | ICD-10: J41-J44 |

| **Table 5. Definitions of prescription medications** | |
| --- | --- |
| **Covariates** | **Definition** |
| Aspirin | B01AC06 |
| Non-aspirin anti-platelet medications | B01AC excluding aspirin (B01AC06) |
| Statins | C10AA |
| Non-statin lipid lowering medications | C10AB, C10AC, C10AD, C10AX01-14 |
| Anticoagulation medications | B01AA, B01AE, B01AF, B01AX |
| Antidiabetic medications | A10 |
| Antihypertensive medications | C02, C03AA-AB, C03BA, C03CA, C03DA, C03EA, C08CA, C08DA, C08DB, C09A, C09BA, C09BB, C09CA, C09DA, C09DB01 |

